#### Secondary outcomes

2.6.2

Secondary outcomes include the time for postoperative abdominal distension to disappear, length of hospital stay, postoperative pain, nausea and vomiting, time to first independent walking, time to first postoperative flatus, time to first postoperative defecation, postoperative complications, and other qualitative indicators for patients.
1.Time for postoperative abdominal distension to disappear: Refers to the difference between the time for postoperative abdominal distension to disappear and the end of the surgery. Patients and their family members should be carefully informed to observe and report the time when the postoperative abdominal distension sensation disappears, and the details should be recorded in the Case Report Form (CRF).2.Postoperative pain, nausea, and vomiting: Postoperative pain and nausea will be assessed using the Visual Analog Scale (VAS). The degree of pain and nausea will be observed and recorded every hour from 1 to 6 h postoperatively and at 24 h, and the frequency of vomiting will be recorded.3.Time to first postoperative flatus: Refers to the difference between the time of the first postoperative flatus and the end of the surgery. Patients and their family members should be carefully informed to observe and report the time of the first postoperative flatus, and the details should be recorded in the CRF.4.Time to first postoperative defecation: Refers to the difference between the time of the first postoperative defecation and the end of the surgery. Patients and their family members should be carefully informed to observe and report the time of the first postoperative defecation, and the details should be recorded in the CRF.5.Length of hospital stay: The time from the end of the surgery to discharge.6.Postoperative complications: Other postoperative complications will be recorded in the CRF.7.Other qualitative indicators for patients.

#### Safety evaluation

2.6.3

The occurrence of adverse events (AEs) will be monitored through patient reports and medical staff evaluations during the study process. Clearly, mild AEs caused by acupuncture will mainly be reported by patients (such as subcutaneous congestion, prolonged acupuncture pain, etc.). Needle extraction bleeding is extremely common in acupuncture operations and has a certain therapeutic effect. Therefore, using dry cotton ball finger pressure to quickly stop mild needle bleeding is not considered an AE. If a serious AE occurs that leads to hospitalization, disability, life-threatening or death, it will be reported to the Ethics Committee within 24 h.

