### Randomization, blinding, and grouping

2.4

The experiment was grouped using SPSS 26.0 (IBM, USA). A random number table was generated, with “0” representing the “EA group” and “1” representing the “EA-sham group.” The grouping results will be written on paper, placed in sealed and opaque envelopes, and kept by a dedicated person. A researcher who did not know the grouping results opened the envelopes in sequence according to the envelope numbers and assigned patients to the corresponding treatment groups, with no one allowed to make unauthorized changes. The study strictly adhered to the three-separation principle of blinding, which means that observation recording, treatment operations, and data analysis were conducted separately. Random grouping was the responsibility of a dedicated person, observation recording was completed by non-operators, treatment operations were carried out according to the envelope grouping, and data statistics and analysis were the responsibility of a dedicated person to ensure the authenticity of clinical records. Patients in both EA groups were unaware of their treatment group.

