##### Procedure

2.5.2.3

All patients are placed in a supine position and the acupoints are routinely disinfected. The 40 mm disposable sterile acupuncture needle (Hwato, Suzhou, China) was used. The needle was directly punctured 0.5∼1 cun (about 15–30 mm). The acupuncture manipulation is reinforcing and reducing to DeQi. The patient may not be fully awakened at the time of the first acupuncture, so we defined DeQi as the sensation of blockage felt by the acupuncturist during the maneuver. After, use an electric wire to connect both sides of ST36, using a continuous wave type with a frequency of 2 Hz and an intensity of 2–3 mA. There were two times of EA interventions, with the first intervention starting after the surgery, and the second intervention lasting 30 min on the morning of the second postoperative day. When taking the needle, gently press with your hand and use a clean cotton pad to prevent bleeding.

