## Limitations

4

In this study, there are certain limitations. Firstly, it is a single-center study, which may limit the generalizability of the study results. Secondly, in our study, we were unable to blind the acupuncturist because the acupuncturists performing the intervention had over ten years of clinical acupuncture experience, which was considered difficult to blind (28), so we did not implement blinding of the acupuncturists.

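### Mild needle-removal bleeding is excluded from the adverse events because it is common and supposedly therapeutic, so minor needling harm is understated in both arms

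*Protocol article*

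**What the plan says.** Section 2.6.3 (Safety evaluation) gives a rule and its reason. The reason is that "Needle extraction bleeding is extremely common in acupuncture operations and has a certain therapeutic effect". The rule drawn from it is that "using dry cotton ball finger pressure to quickly stop mild needle bleeding is not considered an AE". The same section keeps congestion under the skin and prolonged needling pain as examples of mild AEs.

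On detection, AEs are to be "monitored through patient reports and medical staff evaluations during the study process", and "mild AEs caused by acupuncture will mainly be reported by patients". Section 2.4 adds that "observation recording was completed by non-operators" and that "Patients in both EA groups were unaware of their treatment group". Section 4 (Limitations) says of the operators: "so we did not implement blinding of the acupuncturists".

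The procedure in 2.5.2.3 has the operator, on withdrawing each needle, "gently press with your hand and use a clean cotton pad to prevent bleeding". Section 2.5.3 gives the sham arm the same intervention about 1.5 cm away from the two points, so both arms are needled and fall under the same rule.

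**The concern.** The AE definition leaves out the one needling event that the article itself describes as extremely frequent, and neither stated reason supports leaving it out. A common event is an expected event; that affects how it is collected and tabulated, not whether it is a harm. Calling it therapeutic assumes benefit in a trial set up to test benefit. It fits the sham arm least of all, because the trial hypothesises that needling there works less well.

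What is at stake is the absolute rate of minor needling harm. The Discussion favours acupuncture over drugs partly because it expects less harm, and section 2.7 presents the study as a pilot for a larger trial. A reader, or the planner of that trial, would take from the AE table a needling-harm rate that omits this event.

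**Working it through.** **There is no plan figure to reproduce.** The article states no bleeding rate, AE rate or safety threshold. The check is therefore a reading of the text, followed by an illustration of scale.

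**Reading the sections together**

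1. *Reason against rule (2.6.3).* Neither frequency nor therapeutic effect bears on whether an event is adverse. The rule also covers the sham arm (2.5.3), where the therapeutic reason is weakest.
2. *Boundary (2.6.3 against 2.5.2.3).* The exclusion needs bleeding to be mild and to stop quickly under finger pressure. The article gives no time, volume or grade for either term. Pressing the site is already a routine part of needle removal, so the use of pressure does not mark out the excluded cases. Only the two undefined words do.
3. *Assessor (2.6.3, 2.4, 4).* Patients and medical staff are the AE sources, non-operators do the recording, patients are blinded and acupuncturists are not. None of these sections says who decides that a bleed was mild and quickly stopped. Section 2.5.2.3 adds that patients may not be fully awake at the first session, which weakens patient report there.
4. *What still counts (2.6.3).* Bleeding that is more than mild or not quickly stopped, congestion under the skin, prolonged needling pain, other AEs and serious AEs all remain.

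**Scale (illustration only)**

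Inputs from the article: 72 patients (2.7), 36 per group (Abstract); bilateral ST36 and PC6, so 4 sites (2.5.2); 2 sessions (2.5.2.3).

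Assumed: a rate p of excluded bleeds per needle removal, from 1% to 20%; independence between removals; all patients completing both sessions.

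- Removals per patient: 4 × 2 = 8. In total: 72 × 8 = 576, or 288 per arm.
- Expected excluded bleeds: 576 × p.
- Patients with at least one: 1 − (1 − p)^8.

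| Assumed p | Expected bleeds | Patients with at least one | Of 72 |
|---|---|---|---|
| 1% | 5.8 | 7.7% | 5.6 |
| 2% | 11.5 | 14.9% | 10.7 |
| 5% | 28.8 | 33.7% | 24.2 |
| 10% | 57.6 | 57.0% | 41.0 |
| 20% | 115.2 | 83.2% | 59.9 |

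If bleeding clusters within patients, the expected counts stay the same but fewer patients are affected than shown.

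Suppose other AEs occur in an assumed 5% of patients, independently of bleeding. Counting every such bleed would then change the any-AE proportion from 5% to 1 − 0.95 × (1 − 0.077) = 12.3% at p = 1%, 37.0% at p = 5% and 59.1% at p = 10%.

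**The case against.** The strongest reply is that this is a prespecified and openly stated threshold. A brief surface bleed that stops under pressure differs from congestion left under the skin, so counting one and not the other is coherent. That stands: the congestion example does not prove an inconsistency. An article may also leave working limits and CRF items to the full protocol. That stands too, so the missing limits for mild and quickly are secondary. The point rests on the rule and the reason, both of which are stated.

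It is also fair that harm is not a stated objective. The aims are efficacy and feasibility, and the article states no safety hypothesis. Low harm appears only as an argument for choosing acupuncture.

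Three stronger readings are tempting and are not supported:

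- *The unblinded acupuncturist decides what counts.* The operator probably sees the bleed first, but 2.6.3 names patients and medical staff and 2.4 gives recording to non-operators. The text supports only that the assessor is not named.
- *Excluded bleeds leave no record.* The article says they are not AEs. It does not say that they go unrecorded, and the CRF is not shown.
- *The rule favours one arm.* Both arms are needled by the same procedure under the same rule. Bias would need the boundary to be applied differently by arm, which nothing in the text shows.

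The rates used for scale are assumptions, and their width shows how little the article fixes.

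**Conclusion.** The point holds as a minor one. Followed as written, the AE definition understates the absolute rate of minor needling harm in both arms, because it drops a very common event for reasons that do not show it to be harmless. The article does not fix the amount. With 8 removals per patient, an assumed 1% to 20% of removals bleeding and independence between removals, about 8% to 83% of patients would have at least one excluded bleed.

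A reader might infer that the whole safety result is low by definition. That goes too far: only bleeding that is both mild and quickly stopped is removed. The conclusion concerns the absolute rate and needs no difference between arms.

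**What to change.** Delete the therapeutic-effect reason from 2.6.3. Mild, quickly stopped bleeding may stay outside the AE listing, but record it at each session as an expected needling event: yes or no per site, and whether pressure was needed beyond a time fixed in advance. Where possible, have the non-operator recorder of section 2.4 make the entry; this also settles who judges it. Report the event by arm and pooled, beside the AE table.

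The cost is one CRF line per session and one table row. The downside is a higher published needling-event rate.

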### Sample size estimation

2.7

The trial is primarily aimed at preliminary testing the feasibility of evaluating the efficacy of acupuncture in treating post-LC abdominal distension using our outcomes. We define this clinical trial as a pilot trial prior to a large sample trial. According to the “Regulations for the Administration of Drug Registration in China” the sample size for exploratory clinical studies should be at least 20–30 cases. Based on the availability of funds, we selected 30 patients, anticipated a 20% dropout rate, and determined a sample size of 72 patients. The results of this study will contribute to calculating the appropriate sample size for further randomized clinical trials.

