**Method:**

This study is a randomized, single-blind, controlled pilot clinical trial. We divided the patients into two groups: Electroacupuncture (EA) meridian acupoint group and EA non-meridian non-acupoint group. During the study period, both groups will receive routine care and education with an anticipated total of 36 individuals in each group. Both groups of patients will be treated with electroacupuncture (EA) after surgery, and in the morning of the day following the operation, with each session lasting 30 min. Specifically, the EA meridian acupoint group had intervention at the bilateral Zusanli (ST36) and Neiguan (PC6) points, while the EA non-meridian non-acupoints group had selected acupoint interventions at about 1.5 cm from ST36 and PC6. We will use the VAS (Visual Analogue Scale) and abdominal distension grading to evaluate the degree of patients’ postoperative abdominal distension 1–6 h and 24 h after surgery to obtain outcome assessments.

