### Statistical analysis

2.8

All statistical analyses will be conducted according to the intention-to-treat (ITT) principle, which includes patients who have received at least one session of EA treatment. All paper-based data will be electronically entered and analyzed using SPSS 26.0 (per-protocol set for robustness analysis of the results). In the statistical description, continuous data will be presented as mean ± standard deviation (M ± SD) or median and interquartile range, while categorical data will be presented as frequencies and percentages. Demographic and other baseline data will be compared using ANOVA and chi-square tests. Kaplan–Meier analysis will be used for key times of primary outcomes and secondary endpoints, and group comparisons will be made using the Breslow (generalized Wilcoxon) test. Differences in the incidence rates of nausea, vomiting, and abdominal distension will be compared using chi-square tests or the Mann–Whitney U test. The occurrence rates and severity of compliance will be analyzed using chi-square tests or the Mann–Whitney U test at a significance level of *α* = 0.05. Missing data will be handled using last observation carried forward and multiple imputation.

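### Section 2.7 allows for 20% dropout by multiplying 30 per group by 1.2, so 72 patients leave about 29 completers per group rather than 30

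*Protocol article*

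**What the plan says.** The protocol article, section 2.7 (Sample size estimation), calls the study a pilot ahead of a larger trial. It cites a Chinese drug-registration regulation under which "the sample size for exploratory clinical studies should be at least 20–30 cases", and then, with funding as the stated constraint, says: "we selected 30 patients, anticipated a 20% dropout rate, and determined a sample size of 72 patients". It does not say whether the 30 is per group or for the whole trial.

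The abstract (Method) supplies the missing piece. It describes two groups, "with an anticipated total of 36 individuals in each group".

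Section 2.7 uses no effect size, standard deviation, power or precision target. Section 2.8 sets tests "at a significance level of *α* = 0.05", but that level plays no part in the choice of 72.

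**The concern.** The sentence gives a starting number, a dropout rate and a result. On the natural reading, 30 is the number wanted after losses, 20% is the share of enrolled patients expected to be lost, and 72 is the enrolment that allows for those losses. The three figures do not fit that reading, because a 20% loss from 72 does not leave 30 in each of two groups.

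The omission of the words per group adds to the difficulty. Taken alone, 30 patients with a 20% allowance cannot produce 72, so the reader has to recover the meaning from the abstract.

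What is at stake is the accuracy of the only calculation offered for the trial's size. Section 2.7 also says the results will inform the sample size of a later trial. If the same multiplication were carried forward at 20% dropout, that trial would expect 1.2 × 0.8 = 0.96 of its target number of completers, a 4% shortfall.

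**Working it through.** **Inputs**

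- Number before the dropout allowance: 30 (section 2.7).
- Dropout: 20% (section 2.7, "anticipated a 20% dropout rate").
- Stated total: 72 (section 2.7, "determined a sample size of 72 patients").
- Two groups of 36 (abstract, Method).

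**Step 1: is 30 per group or in total?** If 30 were the trial total, the allowance would give 30 × 1.2 = 36 or 30 / 0.8 = 37.5 (38) patients in the whole trial. Neither is 72. The 30 must therefore be per group. This is an inference, but no other reading of the sentence gives the stated total.

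**Step 2: reproduce the stated figure.** 30 × (1 + 0.20) = 36 per group, and 2 × 36 = 72. The match is exact, including the abstract's 36.

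**Step 3: apply the stated dropout to the stated enrolment.** 36 × (1 − 0.20) = 28.8 completers per group, and 72 × 0.80 = 57.6 in total. Against 30 and 60, the expected shortfall is 1.2 per group and 2.4 in total.

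**Step 4: the enrolment that fits a 20% dropout rate.** 30 / (1 − 0.20) = 37.5, rounded up to 38 per group, or 76 in total. Inflating the total first gives 60 / 0.80 = 75, which does not split evenly into two groups.

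**Step 5: the dropout rate at which 36 leaves 30.** 1 − 30/36 = 16.7%.

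**Step 6: how often the target would be reached.** Assume that each patient drops out independently with probability 20%; the documents do not state this. The binomial probability that a group of 36 keeps at least 30 is then 0.40, and that both groups do is 0.40² = 0.16. With 38 per group, the single-group probability is 0.66. The gap in expected numbers is small, but on the plan's own rate a group of 36 is more likely than not to finish below 30.

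**The case against.** The case on the other side accepts the arithmetic and disputes its consequence. Most of it stands.

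- **Nothing depends on 30.** Section 2.7 never says that 30 patients must complete, and no power, precision or decision rule is tied to that number. A reader might infer that the trial is underpowered as a result. The documents do not support this: no power is claimed, and the size is presented as a pilot size set by funds.
- **The cited minimum is not breached.** A reader might infer that the trial falls below its own regulatory floor. The cited figure is a range of 20 to 30 cases, and 28.8 lies inside it. The article does not say whether the range applies per group or in total. If in total, 57.6 is well above it.
- **Dropout is not the same as loss from the analysis.** A reader might infer that only 28.8 per group will be analysed. Section 2.8 builds the main analysis on patients who had at least one electroacupuncture session and handles missing values by last observation carried forward and multiple imputation; the per-protocol set serves only as a robustness check. Someone who leaves after the first session stays in the main analysis. Section 2.3.3 does eliminate some patients after randomization, for instance after conversion to open surgery, so some losses may reach the analysis. The document does not let one say how many.
- **The rate is a round guess.** The article gives no source for 20%, and a true rate of 16.7% would remove the gap. This shows how small the matter is. It does not make the sentence right, because the sentence states 20% and calls it a dropout rate, which is not the same as an enrolment margin of 20%.
- **The abstract settles the per-group question.** It does, for a reader who consults it, so the missing words are an editorial slip.

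**Conclusion.** The sentence is wrong as written, and the error is minor. The plan multiplied 30 per group by 1.2 where its stated dropout rate calls for division by 0.8. At 20% dropout, 72 enrolled patients leave about 28.8 completers per group (57.6 in total), which is 1.2 per group and 2.4 in total short of the number the calculation started from.

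The conclusion rests on two readings: that 30 is per group, which is the only reading that gives 72, and that 30 is meant as the number remaining after dropout, which is the natural purpose of such an allowance but is not spelled out.

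It does not extend to the validity of the trial, to any loss of stated power, to a breach of the cited range, or to the number in the main analysis. It is a correction to the number of completers the reader should expect.

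**What to change.** Keep 72 and restate the sentence in section 2.7 along these lines:

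> 30 patients per group were targeted; 36 per group (72 in total) are enrolled, which leaves about 29 completers per group (about 58 in total) at 20% dropout, or 30 per group if dropout does not exceed 16.7%.

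This also adds the missing per-group wording and brings section 2.7 into line with the abstract. The cost is one sentence: no additional patients or funds, and no change to design or analysis. The expected number of completers reads slightly lower than before.

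If an expected 30 completers per group at 20% dropout is in fact wanted, enrolment would have to be 38 per group (76 in total), four more patients than planned. Nothing in the document requires that, and funding is its stated constraint. In either case, the later trial's sample size should divide by one minus the dropout rate.

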### Statistical analysis

2.8

All statistical analyses will be conducted according to the intention-to-treat (ITT) principle, which includes patients who have received at least one session of EA treatment. All paper-based data will be electronically entered and analyzed using SPSS 26.0 (per-protocol set for robustness analysis of the results). In the statistical description, continuous data will be presented as mean ± standard deviation (M ± SD) or median and interquartile range, while categorical data will be presented as frequencies and percentages. Demographic and other baseline data will be compared using ANOVA and chi-square tests. Kaplan–Meier analysis will be used for key times of primary outcomes and secondary endpoints, and group comparisons will be made using the Breslow (generalized Wilcoxon) test. Differences in the incidence rates of nausea, vomiting, and abdominal distension will be compared using chi-square tests or the Mann–Whitney U test. The occurrence rates and severity of compliance will be analyzed using chi-square tests or the Mann–Whitney U test at a significance level of *α* = 0.05. Missing data will be handled using last observation carried forward and multiple imputation.

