#### Exclusion criteria

2.3.2

1. Patients requiring simultaneous combined procedures;2. Patients experiencing severe intraoperative or postoperative complications requiring intensive care;3. Patients using medications affecting the intestines (e.g., Chinese herbal medicine) within one month;4. Patients who have undergone acupuncture treatment within six months;5. Patients with cardiac pacemakers;6. Patients currently participating in other clinical studies within six months;7. Patients with a history of syncope, epilepsy, or psychiatric disorders;8. Patients undergoing epidural anesthesia;

Meeting any of the above criteria will result in exclusion.

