#### Eliminate and detachment criteria

2.3.3

Patients meeting the following criteria during the study will be eliminated:
1.Those found to not meet the above diagnosis and inclusion criteria after randomization;2.Patients were converted to open surgery intraoperatively or diagnosed with other disorders intraoperatively and postoperatively.3.Patients with poor compliance who fail to receive acupuncture treatment as prescribed;4.Patients experiencing severe adverse reactions, complications, and special physiological changes that make it inappropriate to continue the trial.Subjects meeting the following criteria during the study will be considered as dropouts:
1.Those found to not meet the inclusion criteria or meet any of the exclusion criteria after randomization;2.Patients requesting to withdraw from the study;3.Patients experiencing intolerable adverse events/serious adverse events, where the investigator judges that the risk of continuing participation in the trial outweighs the benefits;4.Patients who lost to follow-up.

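### The set labelled ITT is a treated set, and the text does not say whether patients eliminated under §2.3.3 stay in the primary analysis

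*Protocol article*

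**What the plan says.** Protocol article, §2.8 Statistical analysis, commits every analysis to the "intention-to-treat (ITT) principle, which includes patients who have received at least one session of EA treatment". It names one other set, "per-protocol set for robustness analysis of the results", without defining it there. Missing data are to be handled by last observation carried forward and multiple imputation.

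§2.3.3 Eliminate and detachment criteria opens with "Patients meeting the following criteria during the study will be eliminated". The list covers:
- "Those found to not meet the above diagnosis and inclusion criteria after randomization"
- "Patients were converted to open surgery intraoperatively or diagnosed with other disorders intraoperatively and postoperatively"
- "Patients with poor compliance who fail to receive acupuncture treatment as prescribed"
- "Patients experiencing severe adverse reactions, complications, and special physiological changes that make it inappropriate to continue the trial"

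A second list in the same section, for dropouts, again contains ineligibility found after randomisation and intolerable or serious adverse events, and adds withdrawal of consent and loss to follow-up.

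§2.3.2 Exclusion criteria, item 2, reads "Patients experiencing severe intraoperative or postoperative complications requiring intensive care". §2.6.2 makes postoperative complications a secondary outcome.

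§2.5.2.3 plans two EA sessions. §2.4 says that patients do not know their group and that people other than the operators record observations. §4 Limitations says that the acupuncturists are not blinded.

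**The concern.** Randomisation makes the two groups comparable only when patients are analysed as allocated, whatever happens to them afterwards. §2.8 uses the ITT name for a set selected on treatment received, so a reader would take it that all 72 randomised patients are compared when the definition does not say so.

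§2.3.3 adds a second uncertainty. Failure to comply, adverse reactions and postoperative complications can all arise after allocation, and an acupuncturist who knows the arm could influence some of them. If meeting a §2.3.3 criterion takes a patient out of the primary comparison, removal can depend on both arm and outcome. That matters in a trial which §2.1 describes as a superiority trial and whose results, according to §2.7, will feed the sample size of the next one.

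**Working it through.** **Planned numbers.** §2.7 takes 30 patients (read as per arm) and a 20% dropout allowance: 2 × 30 × 1.2 = 72, or 36 per arm, which matches the stated total and the Abstract. If 20% of patients were left out of the analysis, 72 × 0.8 = 57.6 would remain (28.8 per arm). The 20% is an anticipated dropout rate. The article gives no elimination rate, power, effect size or SD.

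**The two rules side by side.**

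| Randomised patient | Set defined in §2.8 | §2.3.3 |
|---|---|---|
| No EA session | Outside | Eliminated if this counts as poor compliance; dropout if the patient withdrew |
| One session, second missed through poor compliance | Inside | Eliminated |
| One or two sessions, then a severe adverse reaction or complication that makes continuing inappropriate | Inside | Eliminated; also a dropout if the event is judged intolerable or serious |
| At least one session, later found not to meet the inclusion criteria | Inside | Eliminated and dropout |

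The first row departs from ITT on any reading. In the other three rows the sections give different answers unless elimination means something other than removal from the primary analysis, and the article does not say what it means. The last two rows also show one patient fitting both lists.

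**Illustration of what is at stake if elimination means removal.** Assumptions, none of them from the article: no true effect, normal outcome with SD 1, 36 per arm, two-sided t-test at 0.05 (§2.8 gives α = 0.05 but not the sidedness), and removal of the patients highest on a latent variable correlated ρ = 0.5 with a worse outcome.

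Removing a fraction p from the upper tail shifts an arm's mean by ρ·φ(z)/(1−p), where z is the (1−p) normal quantile. The ratio φ(z)/(1−p) is 0.109 at 5% and 0.350 at 20%. The bias for 5% against 20% is therefore 0.5 × (0.350 − 0.109) ≈ 0.12 SD.

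Simulation (10,000 to 40,000 replicates per setting) gives:

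| Removed, arm 1 / arm 2 | Bias (SD) | Type I error |
|---|---|---|
| 5% / 20% | 0.12 | 7.5–7.8% |
| 5% / 25% | 0.16 | 9.1–9.7% |
| 10% / 30% | 0.15 | 8.8–9.2% |
| 20% / 20% | 0.00 | 4.8–4.9% |

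The inflation comes from unequal removal. Equal removal under the same mechanism leaves the error rate at its nominal level and costs only precision. The simulation does not model the one-session rule.

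**The case against.** The strongest reply is that the article never defines elimination as removal from the primary analysis. §2.8 has a per-protocol set, and its imputation methods make sense only if patients with incomplete data are kept. On that reading §2.3.3 governs withdrawal from treatment or the per-protocol set, and a patient with one session stays in the primary comparison. This is a fair reading and it stands. A reader might infer that the main comparison is certain to drop non-compliant and complicated cases; the text does not establish that. It leaves the matter open, and for that reason the sections need reconciling.

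Three other stronger inferences are not supported:

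- **Harms deleted.** A reader might conclude that severe complications vanish from the report. §2.6.2 records complications in the CRF, and §2.6.3 monitors adverse events and reports serious ones to the Ethics Committee within 24 h. Nothing says that eliminated patients' safety data are discarded. What remains is the tension between exclusion criterion 2 and the complications outcome.
- **Randomisation before the end of surgery.** The conversion criterion might suggest this. But participation begins with preoperative consent and baseline data (§2.2), §2.4 does not say when envelopes are opened, and the flow chart is not shown. Conversions could fall before allocation.
- **Large bias.** Both arms receive EA at nearby sites, patients are blinded and non-operators record the observations. The article gives no reason to expect a four- to five-fold difference in removal between arms.

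The pilot status in §2.7 lowers the stakes but does not excuse the label, because §2.1 sets a superiority hypothesis.

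**Conclusion.** The point holds in limited form. Two things are certain from the text: the set called ITT is restricted to patients who had at least one EA session, and §2.3.3 and §2.8 give no single answer for a patient treated once and then eliminated. The overlap between the elimination and dropout lists is also plain.

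The size is uncertain. Bias from the one-session rule alone is probably modest, since missing the first session should depend little on arm when patients are blinded and both groups receive EA. The figures of about 0.12–0.16 SD and 8–10% type I error apply only if elimination means removal from the primary analysis and removal is as unequal (5% against 20–25%) and as outcome-related (correlation 0.5) as assumed.

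**What to change.** 1. In §2.8, define the primary set as all randomised patients analysed in their allocated group. Keep the at-least-one-session set as a sensitivity analysis, named as modified ITT.
2. In §2.3.3, state that the criteria define only discontinuation of study treatment or exclusion from the per-protocol set, and that outcome and safety data are still collected and analysed. Merge the two overlapping lists so that each patient has one status.
3. Analyse safety in everyone who received any EA, without eliminations.
4. Reconcile exclusion criterion 2 in §2.3.2 with postoperative complications as a secondary outcome in §2.6.2, so that complications occurring after randomisation are counted. How the eligibility rule itself should read is for the investigators.

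The cost is wording in §2.3.2, §2.3.3, §2.6 and §2.8, plus continued data collection on patients who stop treatment. The randomised number stays at 72. The downside is that a few non-compliant or untreated patients remain in the primary set, which slightly dilutes the contrast; the sensitivity and per-protocol analyses will show by how much.
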